## Abstract

**Introduction:**

Based on the advances in the treatment of multiple sclerosis (MS), currently available disease-modifying treatments (DMT) have positively influenced the disease course of MS. However, the efficacy of DMT is highly variable and increasing treatment efficacy comes with a more severe risk profile. Hence, the unmet need for safer and more selective treatments remains. Specifically restoring immune tolerance towards myelin antigens may provide an attractive alternative. In this respect, antigen-specific tolerisation with autologous tolerogenic dendritic cells (tolDC) is a promising approach.

**Methods and analysis:**

Here, we will evaluate the clinical use of tolDC in a well-defined population of MS patients in two phase I clinical trials. In doing so, we aim to compare two ways of tolDC administration, namely intradermal and intranodal. The cells will be injected at consecutive intervals in three cohorts receiving incremental doses of tolDC, according to a best-of-five design. The primary objective is to assess the safety and feasibility of tolDC administration. For safety, the number of adverse events including MRI and clinical outcomes will be assessed. For feasibility, successful production of tolDC will be determined. Secondary endpoints include clinical and MRI outcome measures. The patients’ immune profile will be assessed to find presumptive evidence for a tolerogenic effect in vivo.

**Ethics and dissemination:**

Ethics approval was obtained for the two phase I clinical trials. The results of the trials will be disseminated in a peer-reviewed journal, at scientific conferences and to patient associations.

**Trial registration numbers:**

NCT02618902 and NCT02903537; EudraCT numbers: 2015-002975-16 and 2015-003541-26.

Strengths and limitations of this studyThe concept of the clinical trials is built on recent advances in the understanding of tolerance induction via cell-based therapy, and the effort made to precisely silence myelin-antigen-specific, putatively deleterious immune responses in the disease.The use of cryopreserved tolerogenic dendritic cells (tolDC) allows production of batches of tolDC, stored in ready-to-use aliquots for the required administrations during the treatment period, thereby reducing variability and global production cost.Harmonisation of clinical, MRI and immunological evaluations of the patients will enable us to compare results between two phase I clinical trials evaluating the safety and feasibility of autologous tolDC administration in patients with active MS.The patients are not randomised across the trials, limiting direct comparison of both routes of administration.

## Introduction

Multiple sclerosis (MS) is the leading cause of non-traumatic disability in young adults and typically presents between the age of 20–40 years, in the prime of a patient’s personal and professional life. The heterogeneity of the disease course in MS, that is, relapsing-remitting or progressive, remains a challenge for patient management and design of clinical trials. According to Lublin *et al*,^1^ MS is categorised as relapsing or progressive. In both forms, disease activity (defined by clinical relapse and/or MRI lesions) and disease progression are measured. To date, more than 10 disease-modifying treatments (DMT) are approved for clinical use in patients with active relapsing-remitting MS (RRMS). This has dramatically influenced the management of MS patients in daily practice and has positively influenced prognosis of of a subset of MS patients. Indeed, whereas earlier epidemiological studies indicated that 50% of patients develop secondary progressive MS after 15 years when untreated,^2^ only 18% of patients treated with modern MS therapeutics were reported to evolve to a secondary progressive course after a median duration of 16.8 years in a recent cohort.^3^ Nonetheless, DMT are not specific nor selective for MS, that is, they work in an immunomodulatory or immunosuppressive way by sequestering or depleting lymphocytes, although that some therapies can induce immune reconstitution as well. Moreover, treatment-related side effects or risks can be severe,^4^ leaving a significant and unmet need for safer and more disease-selective treatments.

The crux of MS is the patient’s own immune cells attacking self-antigens in the central nervous system (CNS), caused by a loss of tolerance against myelin antigens. This is manifested by inflammatory infiltrates, demyelination and axonal loss, resulting in the clinical symptoms of the disease.^5 6^ Previously, it was shown that proteins expressed in the myelin sheath, protecting neuronal axons of the CNS, are an important target of the autoreactive T cell response.^7–9^ Also in our hands, ex vivo T cell reactivity against a mix of seven immunodominant myelin-derived peptides could be demonstrated in RRMS patients as compared with healthy controls and patients with other neurological disorders.^10^ Although the underlying cause of the loss of tolerance towards myelin antigens has not been elucidated yet, one ultimate aim in the treatment of MS is to reestablish antigen-specific immune tolerance towards CNS structures.^11–15^ In this perspective, it is postulated that tolerance-inducing antigen-specific therapy can be an innovative and promising strategy for the treatment of autoimmunity. This approach is based on the possibility that autoreactive B and T cells, driving myelin destruction and damage in the CNS, will be eradicated by inducing tolerance to myelin-derived peptides, without interfering with protective immunity. Several approaches involving the induction of antigen-specific tolerance have reached the clinical development phase and demonstrated promising results in phase I/II clinical trials (extensively reviewed by Willekens and Cools).^12^ Given the fact that dendritic cells (DC) play a key role in controlling the immune response by steering the outcome of antigen presentation to T cells, the use of tolerance-inducing or tolerogenic dendritic cells (tolDC) may provide prospect for the treatment of MS.^16–20^ Recently, we demonstrated the potential of 1α,25-dihydroxyvitamin D_3_ to generate tolDC from MS patients.^21–23^ Indeed, vitamin D_3_-treated tolDC from MS patients display a maturation-resistant phenotype, that is, they maintain their low expression levels of costimulatory molecules (CD80, CD83 and CD86) and anti-inflammatory cytokine profile, even following rechallenge with an inflammatory stimulus such as lipopolysaccharide. Furthermore, tolDC from MS patients are capable of inducing stable and antigen-specific T cell hyporesponsiveness. After in vitro stimulation with myelin-derived peptide-pulsed vitamin D_3_-treated tolDC, T cells were unresponsive to the myelin peptides used, while retaining their capacity to respond to an unrelated antigen. Moreover, T cell hyporesponsiveness was robust, as T cells were not reactivated after rechallenge with immunostimulatory DC.^21–23^

Also in vivo, the administration of bone marrow-derived vitamin D_3_-treated tolDC pulsed with MOG_40-55_ has been shown to induce antigen-specific T cell tolerance in experimental autoimmune encephalomyelitis (EAE), the animal model of MS. Mice treated with MOG_40-55_-pulsed bone marrow-derived vitamin D_3_-treated tolDC before disease induction showed reduced incidence of the disease. Furthermore, when the treatment was used therapeutically in mice already showing clinical signs of the disease, the severity of the disease was significantly reduced.^24^ However, repetitive injections of tolDC were necessary for a prolonged clinical effect in EAE. In this context, cryopreserved MOG_40-55_-pulsed tolDC demonstrated similar clinical benefit compared with fresh tolDC, underlining the therapeutic potential and clinical applicability of cryopreserved tolDC.^21 25^

Recently, a number of phase I studies investigating the safety and feasibility of tolDC therapy for autoimmune diseases such as rheumatoid arthritis, type I diabetes or Crohn’s disease were completed (table 1).^18^ The first results are highly encouraging since none of the trials found safety concerns related to tolDC administration in these patients. TolDC were well tolerated and autoimmunity was not exacerbated in the patients treated.^26–29^ Nevertheless, numerous questions remain, and the efficacy of antigen-specific tolDC therapy may depend on many factors, of which the route of administration is among the most important. When considering the route of delivery of DC, one needs to take into account that different routes lead to different sites of accumulation of the vaccinated DC. In most clinical studies to date, ex vivo generated DC were injected either intravenously, intradermally or subcutaneously. In humans, migration of DC towards the secondary lymph nodes is superior after intradermal injection compared with after subcutaneous injection of DC,^30–32^ whereas migration of intravenously injected DC has not been monitored so far. Direct delivery of DC to lymph nodes via intranodal injection showed promising results in therapies using immunostimulatory DC in cancer,^33 34^ but has not been evaluated for tolDC. It was demonstrated that brain-derived antigens can be drained from the interstitial or cerebrospinal fluid via the *lamina cribrosa* and nasal mucosa to the cervical lymph nodes, indicating that the cervical lymph nodes could be one of the first stations for the antigenic presentation at the peripheral level.^35 36^ Hence, we hypothesise that intranodal injection of tolDC directly interferes with the antigen presentation and consequently, the stimulation and proliferation of autoreactive T cells. Furthermore, this route of administration omits the need for the migration requirements of the tolDC, thereby potentially enhancing the efficacy of the vaccine. Although intranodal injection is more complex, requiring ultrasound guidance, this technique is part of the daily practice at the endocrinology or radiology department of most reference hospitals.

**Table 1 T1:** Overview of clinical trials using tolDC as therapeutic intervention in autoimmune diseases

Reference	Indication	Study design	Number of patients	Cell product and control condition	Dose	Administration mode	Primary outcome measure	Results	Immunological effects
Zubizarreta *et al* 44 2019	MS and NMO	open-label, dose-escalation, phase Ib	8 MS and 4 NMO	autologous tolDC loaded with either myelin peptides or AQP4	50×10^6^, 100×10^6^, 150×10^6^, and 300×10^6^ tolDC in total, separated in three independent doses administered every 2 weeks	intravenous	safety and tolerability	well tolerated no serious adverse events	↑ IL-10 production in peptide-stimulated PBMCs and ↑ in the frequency of Tr1
Bell *et al* 28 2017	Inflammatory arthritis	unblinded, dose-escalation, randomised, phase I	9	autologous tolDC loaded with autologous synovial fluid as a source of autoantigens	1×10^6^, 3×10^6^ or 10×10^6^ tolDC arthroscopically vs saline only	intra-articular	flare of disease in the target knee within 5 days of treatment	no target knee flares within 5 days of treatment	no consistent immunomodulatory effects in peripheral blood
Benham *et al* 27 2015	Rheumatoid arthritis	open-label, controlled, phase I	34	autologous DCs modified with a nuclear factor kappaB (NF-kappaB) inhibitor exposed to four citrullinated peptide antigens, designated “Rheumavax,”	a low dose of 1×10^6^ DCs and a high dose of 5×10^6^	intradermal	safety	mild adverse events	↑ in effector T cells and an ↑ ratio of regulatory to effector T cells; ↓ in serum interleukin-15 (IL-15), IL-29, CX3CL1, and CXCL11; ↓ T cell IL-6 responses to vimentin _447-455_-Cit450 relative to controls
Jauregui-Amezaga *et al* 29 2015	Crohn's disease	open-label, dose-escalation, phase I	9	autologous tolDC	first three cohorts: a single injection of 2×10^6^, 5 x 10^6^ or 10 x 10^6^ tolDC; last three cohorts: 3 bi-weekly injections (same dose escalation schedule)	intraperitoneal	safety	no adverse effects	
Giannoukakis *et al* 26 2011	Diabetes type 1	randomised, double-blind, phase I	10	autologous unmanipulated dendritic cells or tolDC	10×10^6^ cells once every 2 weeks for a total of four administrations	intradermal	safety	no adverse effects	↑ in the frequency of peripheral B220+CD11c- B cells

CXCL, Chemokine Ligand; DC, dendritic cells; Il, Interleukin; MS, multiple sclerosis; NMO, neuromyelitis optica; PBMC, Peripheral Blood Mononuclear Cell; tolDC, tolerogenic dendritic cells; Tr1, Regulatory T-cell type.

Until now, there are no available data showing superiority of one route over others for the administration of peptide-loaded tolDC. Here, we will compare intradermal injection to intranodal injection. Only the direct comparison of these different routes of administration in two dose-escalation studies will allow us to determine if both routes are equally safe.

In conclusion, our objectives are to evaluate safety, clinical feasibility and the immunological consequences of peptide-loaded tolDC administered intranodal or intradermal in MS patients in two clinical trials. Harmonisation of the procedures for clinical, MRI as well as immune-monitoring will enable us to compare results between trials of which the study protocols will be discussed in detail here.

## Methods and analysis

### Study design

Two open-label, dose-escalation phase I clinical trials, MS-tolDC and TOLERVIT-MS, are designed in a coordinated and comprehensive manner and run simultaneously in Belgium (Antwerp University Hospital, Edegem) and Spain (Hospital Germans Trias i Pujol, Badalona), respectively. Patient recruitment started mid-2017 and is anticipated to end in 2020.

#### Primary objectives

To evaluate the safety of administering tolDC, the occurrence and severity of adverse events (AE) will be recorded. To assess feasibility, successful production of tolDC according to good manufacturing practices (GMP) starting from a leukapheresis procedure will be assessed.

#### Secondary objectives

Preliminary efficacy measures, including clinical outcomes and brain MRI, will be evaluated. In addition, whole blood lymphocyte phenotyping and cytokine profiling will be assessed before and after completion of the vaccination cycle, as well as the ability of tolDC to suppress pathogenic T cell responses. For this, myelin-specific T cell reactivity will be determined before and after completion of the vaccination cycle. All secondary objectives contribute to determination of proof of principle.

#### Patient reported outcome measurements

Multiple Sclerosis Quality of Life-54 37 will be evaluated to detect changes in general and disease-specific quality of life.

#### Patient and public involvement

This study was inspired by the unmet need of finding a cure for MS, which is a key priority recognised by both patients and neurologists.^38^ While patients were not involved in the design of the clinical trial, they are involved in the conduct of the study. In fact, in order to spread awareness and information about the clinical trials and its results beyond the research community with the public as a whole, a stakeholder committee was installed consisting of experts from major interest groups including members of the Flemish, Belgian and Spanish MS societies as well as Flemish and Spanish MS patients. This stakeholder committee will accompany the clinical trials from the start to the end. It has several aims: (i) to keep the stakeholder informed, (ii) to ensure that their views are considered, (iii) to challenge the project by the identification of potential emerging needs and (iv) to play an active part in the dissemination and the use of the project’s results.

### Study population

#### Eligibility and enrolment

Patients with active relapsing-remitting and active progressive MS, diagnosed according to most recent McDonald criteria,^39 40^ and who are not eligible for or do not want to be treated with currently available DMT, will be recruited. Patients are included after written informed consent and enrolled in the study when the inclusion and exclusion criteria are met (table 2).

**Table 2 T2:** Inclusion and exclusion criteria. All the inclusion criteria must be fulfilled. The presence of any of the exclusion criteria shall exclude the patient

Inclusion criteria	Exclusion criteria
MS according to most recent McDonald criteria	Previous use of immunosuppressive or cytostatic treatment, including mitoxantrone, cladribine, alemtuzumab or bone marrow transplantation or stem cell transplantation at any time prior to enrolment
Age 18–60 years	Treatment with fingolimod or natalizumab or dimethylfumarate in the past 12 weeks or teriflunomide within the past 15 weeks or ocrelizumab/rituximab within the past 6 months prior to the first administration
EDSS of 0–6.5 inclusive	Pregnancy or planning pregnancy in the next 12 months and breast feeding
First signs or symptoms at least 3 months prior to enrolment in the study	Drug or alcohol abuse
Active MS (relapsing and/or progressive): one relapse in the past year and/or at least one enhancing lesion on brain MRI in the past year; at least one new or enlarging T2 lesion in comparison with a reference scan from maximum 1 year before	Inability to undergo MRI assessments
Normal peripheral B-cell count after treatment with ocrelizumab	
No evidence of relapse for at least 30 days prior to start of screening and throughout during the screening phase	History of or actual signs of immunodeficiency or malignancies
Positive T cell reactivity response to a mix of seven myelin-derived peptides	Concurrent clinically relevant cardiac, immunological, pulmonary, neurological, renal or other major disease
Able to sign informed consent and comply with the protocol assessments	Active or chronic infection (hepatitis B or C, HIV, syphilis or tuberculosis)
No wish to be treated with currently available DMT	Splenectomy
Appropriate venous access and *adequate cervical lymph nodes on ultrasound mapping	
Use of adequate contraceptive measures. Women of childbearing potential can only be included in the study following use of adequate contraceptive measures. Accepted methods of contraception include use of hormonal contraceptives (oral, intravaginal, intrauterine or transdermal), intrauterine devices, sterilisation or postmenopausal status, use of condoms with spermicide.	

*Only in TOLERVIT-MS.

DMT, disease-modifying treatments; EDSS, Expanded Disability Status Scale; MRI, Magnetic Resonance Imaging; MS, multiple sclerosis.

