#### Determination of sample size and dose-escalation procedure

The studies will be conducted according to a ‘best of five’ design,^41^ an alternative of the traditional 3+3 design in that one additional patient is added when one or even two dose-limiting toxicities (DLT) are observed among the first three patients. Another patient is added when two DLT are observed among four treated patients. Dose escalation is allowed if DLT are observed among none of three, one of four or two of five patients, but the trial will terminate if three or more DLT are observed. A DLT is defined as a serious adverse event (SAE) that is attributable to the study cells administered, or of which the severity prevents further escalation. Dose escalation decisions will be made after all subjects in the cohort have completed at least 3 months of follow-up and when the results of the safety and tolerability analyses of the preceding dose regimen are satisfactory in the judgement of the investigators and the independent Data Safety Monitoring Board (DSMB).

An overview of the dose escalation is provided in table 3. Altogether, each phase I study is intended to accrue a total number of 9–15 evaluable patients.

**Table 3 T3:** Outline of the cell doses and patient numbers, per phase I clinical trial, in the dose escalation cohorts for intradermal and intranodal administration of tolDC

Cohort	Treatment regimen	Patient numbers
1	6 i.d./i.n. injections of 5×10^6^ tolDC	N=3 (+1+1)
2	6 i.d./i.n. injections of 10×10^6^ tolDC	N=3 (+1+1)
3	6 i.d./i.n. injections of 15×10^6^ tolDC	N=3 (+1+1)

N, number; i.d., intradermal; i.n., intranodal; tolDC, tolerogenic dendritic cells.

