### Secondary outcome measures

#### Clinical evaluation

The following clinical and laboratory assessments will be performed during a complete physical examination: vital signs, ECG, routine blood and urine samples, urine pregnancy test in female patients of reproductive potential and serological screening tests, according to the study schedule (figure 1 and table 4). Concurrent drug use or new AE will be reviewed and recorded.

EDSS is based on a standardised neurological examination and measures impairments in eight functional systems, including vision, brainstem, pyramidal, cerebellar, sensory, bowel and bladder, mental (cerebral) and ambulation. It has been used for over 20 years as a clinical outcome measure of MS disease progression and consists of a 10-point scale of disease severity ranging from 0, that is, no disability, to 10, that is, death from MS.^42^ All neurologists involved in patient evaluation will be EDSS training certified.

EDSS will be supplemented by three well-known, quantitative, continuous tests that evaluate ambulation (walking speed by the timed 25 foot walk test or T25FW, arm dexterity and function by the 9 Hole Peg Test or 9-HPT, and cognition by the Symbol Digit Modalities Test or SDMT).

The effect on disability progression will be characterised by reporting the proportion of patients who are free from disease progression. For this, disability will be assessed based on a sustained clinically relevant change seen in any one of the disability assessments: EDSS, T25FW, SDMT or the 9-HTP. Disease progression is defined by: 3-month sustained increase from baseline in the EDSS score (1 point in patients with baseline EDSS score 0 to 5.0; 0.5 point in patients with baseline EDSS score of 5.5–6.5) or 3-month sustained increase of at least 20% from baseline in the time taken to complete the T25FW or 3-month sustained increase of at least 20% from baseline in the time taken to complete the 9-HPT. Percent change from baseline after treatment in SDMT score will also be recorded.

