### Analysis

Given the design of the study (phase I) and its specific primary end point (safety), no confirmatory statistical testing will be performed. P-values will be calculated but interpreted with caution. Study investigations will be exploratory and conclusions will be based on the complete set of patient evidence.

Analyses of safety variables will be performed with the safety population (all the patients treated with at least one dose of the cell product) by available data only analysis. For demographic and safety analysis, that is, the incidence of AE, laboratory values and changes in vital signs, descriptive statistics will be calculated including frequencies for categorical variables and mean and SD, or median and IQR for quantitative parameters. In brief, EDSS and other repeatedly measured variables will be analysed by means of Mixed Models for Repeated Measurements. In case model assumptions are violated (eg, non-Gaussian errors) or when dealing with ordinal efficacy variables, alternative methods (including non-parametric methods and ordinal regression methods for repeated measurements) will be used. The percentage of patients with 1-point in EDSS improvement will be estimated using a binomial regression model including the treatment and the baseline EDSS. The remainder of variables will be analysed according to the appropriate statistical test: χ^2^ or Fisher’s exact test to compare categorical variables, the dependent or independent t-test for continuous Gaussian-distributed variables and the Wilcoxon or Mann-Whitney test for ordinal and non-Gaussian continuous data. The significance level alpha will be set at 0.05 for two-tailed analysis. Variables to assess the analysis of secondary and tertiary outcome measures will be performed with per protocol population. Continuous variables as a minimum will be described by number of total and non-missing observations (n) and the appropriate location-scale statistics including arithmetic mean, SD, minimum, median, Q1–Q3 and maximum. Categorical variables will be presented using the number of non-missing observations (n) or the number of patients in the population (N) as applicable and percentages (%). Two-sided 95% (exact) CI will be provided when relevant.

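### The 1-point EDSS improvement percentage has no minimum baseline, although EDSS 0 is eligible; any patient entering below 1.0 cannot respond but is counted in the denominator

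*Protocol article*

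**What the plan says.** Three statements in the protocol article bear on this point.

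- Eligibility and enrolment, Table 2: patients are admitted with "EDSS of 0–6.5 inclusive". Active disease is defined there by relapse or MRI activity, not by a minimum level of disability, so it does not exclude a patient at EDSS 0.
- Clinical evaluation: EDSS is described as a "10-point scale of disease severity ranging from 0, that is, no disability, to 10, that is, death from MS". The progression rule in the same section uses a step of "1 point in patients with baseline EDSS score 0 to 5.0; 0.5 point in patients with baseline EDSS score of 5.5–6.5", so the article itself provides for patients who start at 0.
- Analysis: "The percentage of patients with 1-point in EDSS improvement will be estimated using a binomial regression model including the treatment and the baseline EDSS". No minimum baseline is attached to this response. The section adds that analysis of "secondary and tertiary outcome measures will be performed with per protocol population", and nothing in the article restricts that population by baseline EDSS.

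On size, "each phase I study is intended to accrue a total number of 9–15 evaluable patients", in three dose cohorts of 3 to 5 patients.

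**The concern.** A 1-point improvement needs at least one point of room above the floor of the scale. A patient entering below 1.0 does not have it, so the non-response is fixed at entry and says nothing about the treatment. Counting these patients mixes two things in one percentage: how often patients who could improve did improve, and how many patients could improve at all.

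With cohorts of 3 to 5 patients, one or two floor patients move the figure visibly. The two trials are not randomised against each other, so their baseline mix may differ, and a gap in the improvement percentage between doses or routes could arise with no difference in effect. The article fixes the responder, the model and the covariate in one sentence, so this is a stated analysis rule and not a detail left open for a later document.

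**Working it through.** **Inputs from the article.** Eligible baseline EDSS 0 to 6.5; scale minimum 0; response is a 1-point improvement; 3 to 5 patients in each of three cohorts. The stated total reproduces: 3 × 3 = 9 and 3 × 5 = 15.

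**Assumptions, not in the article.** k is the number of patients entering below EDSS 1.0. p is the response rate among patients able to respond, taken as 20%, 30% or 40%.

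**Step 1: effect on the percentage.** Expected percentage = p × (n − k)/n. Highest attainable percentage = (n − k)/n.

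| n | k | p = 20% | p = 30% | p = 40% | Maximum |
|---|---|---|---|---|---|
| 9 | 0 | 20.0% | 30.0% | 40.0% | 100% |
| 9 | 1 | 17.8% | 26.7% | 35.6% | 88.9% |
| 9 | 2 | 15.6% | 23.3% | 31.1% | 77.8% |
| 9 | 3 | 13.3% | 20.0% | 26.7% | 66.7% |
| 15 | 1 | 18.7% | 28.0% | 37.3% | 93.3% |
| 15 | 2 | 17.3% | 26.0% | 34.7% | 86.7% |
| 15 | 3 | 16.0% | 24.0% | 32.0% | 80.0% |

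For n = 9, k = 2, p = 30%: 0.30 × 7/9 = 23.3%. In a cohort of 3 with p = 30%, one floor patient gives 0.30 × 2/3 = 20% with a maximum of 67%, and two give 0.30 × 1/3 = 10% with a maximum of 33%.

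**Step 2: does the baseline covariate repair it?** Take two groups of 12. In both, every patient at EDSS 1.0 or above responds with probability 30%, and those patients are spread evenly over 1.0 to 6.5 in half-point steps. One group has no floor patients. The other has k patients at EDSS 0, whose response probability is 0. Among patients able to respond, the true odds ratio is 1. A large-sample logistic fit of response on group and linear baseline EDSS gives:

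| k of 12 | Crude odds ratio | Adjusted odds ratio |
|---|---|---|
| 1 | 0.89 | 0.90 |
| 2 | 0.78 | 0.83 |
| 3 | 0.68 | 0.76 |
| 4 | 0.58 | 0.70 |

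The covariate moves the estimate towards 1 but does not reach it. The reason shows in a single-group fit with score 0 and the scores 1.0 to 6.5 equally frequent and a 30% response above the floor. The linear term predicts 21% at EDSS 0, where the truth is 0, and 34% at EDSS 6.5, where the truth is 30%. If the model is fitted only to patients at 1.0 or above, the odds ratio in the two-group example is 1 by construction.

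**Step 3: size against the uncertainty.** Observed percentages with exact 95% intervals, floor patients kept and then removed:

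- 3 responders of 9: 33.3% (7.5 to 70.1). With one floor patient removed, 3/8 = 37.5% (8.5 to 75.5); with two, 3/7 = 42.9% (9.9 to 81.6); with three, 3/6 = 50.0% (11.8 to 88.2).
- 4 responders of 15: 26.7% (7.8 to 55.1). With two removed, 4/13 = 30.8% (9.1 to 61.4).

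**The case against.** The best case for the plan has several parts.

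- **The effect is conditional.** The article gives no expected baseline EDSS, and if nobody enters below 1.0 the percentage is unaffected. This stands. A reader might infer that the reported percentage is biased downward as a matter of fact; the documents do not support that. The share of all analysed patients who improve is also a legitimate description. It answers a different question from the share among those able to improve.
- **Baseline EDSS is in the model.** This stands in part. The form of the term is not stated, and a categorical term or one separating the floor would behave differently from the linear one tested above. A linear term leaves most of the false difference in place in the example.
- **The endpoint carries little weight.** This stands. The section rules out confirmatory testing and bases conclusions on all the patient evidence. The disability outcome defined under Clinical evaluation is freedom from progression, on which a patient at EDSS 0 can be assessed. Step 3 shows shifts well inside the intervals.

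Three stronger readings are tempting and should not be drawn.

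- Floor patients tilt the fitted baseline slope upward, so a reader might conclude that the plan would report greater benefit in more disabled patients. The plan describes no interpretation of that slope and no treatment-by-baseline interaction. A tilt in its sign shows no misleading conclusion.
- The Discussion says dose and route will be selected from the results of the two trials. It does not name this percentage as a criterion, and escalation rests on dose-limiting toxicity and safety, so a distorted choice of dose or route is not shown.
- The progression rule uses "0.5 point in patients with baseline EDSS score of 5.5–6.5", while improvement needs a full point at every baseline. Nothing in the article requires the two directions to match, so this is not a contradiction.

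**Conclusion.** The point holds as a limited, conditional defect in the Analysis sentence. The eligibility range itself is not wrong. The rule keeps in the denominator any patient who cannot meet the response definition, and a linear baseline adjustment would correct this only partly. Under an assumed 30% response among those able to improve, 1 to 3 floor patients of 9 lower the percentage by about 3 to 10 points. The adjusted odds ratios of 0.90 to 0.70 rest further on an assumed even spread of baseline scores, groups of 12, all floor patients being in one group, and a logistic model with a linear term. No sample size, error rate or escalation rule depends on this endpoint. The case for acting is that the correction costs almost nothing and is best fixed before the data are seen: with three floor patients, choosing the denominator afterwards could turn 3/9 (33%) into 3/6 (50%).

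**What to change.** In the Analysis section, state that the 1-point improvement percentage is estimated, and the binomial model fitted, among patients with baseline EDSS of at least 1.0. State how many patients are left out, by cohort and trial, and show the all-patient percentage beside the restricted one. Eligibility, the 1-point step and the progression definition need no change.

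The cost is about one sentence and no new data. The downside is a slightly smaller denominator and somewhat wider intervals for this one exploratory percentage. If no patient enters below 1.0, the two percentages are identical.
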